### Safety assessment

Adverse events and serious adverse events will be defined according to standard regulatory criteria. Site investigators and research coordinators will prospectively collect safety data through daily review of medical records and direct communication with treating clinicians. The severity, seriousness and causality of each event will be assessed by the local investigator. Prespecified adverse events that will be reported besides death within 28 days of randomisation in hospital are atrial arrhythmia, ventricular arrhythmia, mesenteric ischemia, myocardial ischemia, Takotsubo cardiomyopathy, renal failure requiring RRT, bilateral digital ischemia, cardiac arrest, ischemic stroke and haemorrhagic stroke (Table 4). Additional adverse events defined as potentially or causally related to the study intervention or are otherwise of concern in the judgement of treating clinician will also be recorded. In keeping with established practice of reporting serious adverse events in critical care trials, those events that are deemed part of the natural course of the primary illness or expected complications of the critical illness are not required to be reported [16, 17]. Serious adverse events meeting reporting criteria will be submitted to the coordinating centre within 24 h of site awareness and reported to the relevant human research ethics committees.

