### Safety events

For new adverse events within 28 days, counts and percentages will be reported with *P*-values using Fisher’s exact test where one or more expected count is < 5 or Pearson’s chi-square test, otherwise (Table 5). Win ratio, which is a relatively new approach, appears to be more useful in analysing composite endpoints with varying degree of severity [20] and is increasingly being used as seen in recent RCTs [21, 22]. The win ratio will be calculated by comparing each patient in the treatment group with each patient in the control group to determine who “wins” based on predefined criteria. It provides a hierarchical assessment by first considering the most critical outcomes, such as mortality, before less critical ones, such as adverse events [20]. Hierarchical endpoint in this trial would be a combination of mortality, haemorrhagic stroke, ischemic stroke, cardiac arrest, myocardial ischemia, mesenteric ischemia, renal failure requiring RRT, ventricular arrhythmia, bilateral digital ischemia, takotsubo cardiomyopathy and atrial arrhythmia. Additionally, a sensitivity analysis for the win ratio will be performed using an alternative hierarchy of outcomes using the following order: death, cardiac arrest, ventricular arrhythmia, haemorrhagic stroke, ischaemic stroke, myocardial ischaemia, mesenteric ischaemia, renal failure requiring RRT, bilateral digital ischaemia, Takotsubo cardiomyopathy and atrial arrhythmia. This analysis will assess the robustness of above findings to different event ordering. In addition to win ratio, the net benefit—which is the difference in the proportion of wins between the two groups—will also be reported.

**Table 5 Tab5:** Adverse events (*N*,%) accrued in hospital within 28 days

	Standard MAP	Individualised MAP	*P* value
Hospital mortality			
Haemorrhagic stroke			
Ischemic stroke			
Cardiac arrest			
Myocardial ischemia			
Mesenteric ischemia			
Renal failure requiring RRT			
Ventricular arrhythmia			
Bilateral digital ischemia			
Takotsubo cardiomyopathy			
Atrial arrhythmia			
Hierarchical composite of above events	Win ratio (95% CI): Net benefit (95% CI):		

*RRT* renal replacement therapy

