### Missing data or incongruent data

Medical records will be used to ascertain all outcomes. Outliers will be interrogated for validity and impact explored via sensitivity analyses. The intention to treat population for the primary and secondary outcomes is all participants as randomised. It is expected that there will be no, or minimal, missing data for the outcomes. Analysis of outcomes will be complete case analysis and is expected to include the entire intention to treat population or very close to the entire population. MAP and percentage MAP deficit may be missing for some timepoints, but the method of analysis for MAP and percentage MAP deficit does not require all observations to be non-missing. Missing APACHE III score, type of shock and site data is not anticipated. The proportion of data defining the subgroups is also expected to be complete or nearly complete and patients with missing data will not be included in any subgroup analysis. To minimise loss to follow-up, each site will designate a coordinator responsible for outcome tracking, and outcome data will be obtained from hospital records or national mortality registries where required.

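### The win-ratio hierarchy is headed by unqualified death in the text but by in-hospital death in Table 5, so a death after discharge and before day 28 can count as survival

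*Protocol article*

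**What the plan says.** Three places in the protocol article bear on the top tier of the hierarchy.

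- **Safety events, text.** The main hierarchy is introduced as "Hierarchical endpoint in this trial would be a combination of mortality, haemorrhagic stroke, ischemic stroke, cardiac arrest", followed by the remaining events. The sensitivity hierarchy is set out "using the following order: death, cardiac arrest, ventricular arrhythmia, haemorrhagic stroke", and so on. Neither sentence gives a setting or a time window for death.
- **Safety events, Table 5.** The title limits the table to events "accrued in hospital within 28 days". The first row is "Hospital mortality". The win ratio and net benefit are reported in the last row, labelled "Hierarchical composite of above events".
- **Safety assessment.** The list of prespecified events is introduced as those reported "besides death within 28 days of randomisation in hospital".

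Elsewhere, death carries no hospital restriction:

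- Under Outcomes, the primary endpoint is any recorded death within 14 days of randomisation.
- The 90-day outcome is all-cause, and time to death through day 90 is computed from the date of death.
- RRT-free days gives −1 to anyone who dies within 28 days.
- Table 1 schedules mortality at days 28 and 90.
- The section on missing data says that "outcome data will be obtained from hospital records or national mortality registries where required".

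**The concern.** A win ratio is meant to settle each pair on the gravest outcome first, and the Safety events section gives that as its reason for using the method. If the top tier is hospital death, a patient discharged on day 12 who dies on day 20 has no death event in the composite. That patient ties at the top tier with a living patient, and beats a living patient who had, say, an atrial arrhythmia in hospital.

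Discharge happens after randomisation, and the trial is open-label. Restricting death to the hospital therefore cuts off the top tier at an event that treatment or clinician behaviour could influence. If post-discharge death is the same in both arms, the result is slightly diluted. If it differs by arm, the safety comparison shifts in a direction that cannot be known in advance.

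**Working it through.** **Reading the definitions side by side**

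| Patient | Primary endpoint | RRT-free days | Win ratio as Table 5 states | Win ratio if the text means any death |
|---|---|---|---|---|
| Discharged, dies day 12 | Death | −1 | Survivor | Death |
| Discharged, dies day 20 | Not an event (after day 14) | −1 | Survivor | Death |
| Dies in hospital, day 20 | Not an event (after day 14) | −1 | Death | Death |

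The first two rows show the conflict. The same death is treated differently in analyses whose windows both include it, and differently under the text and the table of one section.

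**Size of the effect**

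The article states no win-ratio figure, so there is none to reproduce. Its sample size of 1260 is used here only to count pairs: 630 per arm gives 630 × 630 = 396,900 pairs.

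Every rate below is an assumption. The model is simplified: death is binary, and the ten non-fatal tiers are collapsed into one. Let p0 and p1 be the proportions counted as dead, and a0 and a1 the non-fatal event rates among those counted as alive (0 = standard, 1 = individualised).

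- Wins = p0(1 − p1) + (1 − p0)(1 − p1) · a0(1 − a1)
- Losses = p1(1 − p0) + (1 − p0)(1 − p1) · a1(1 − a0)
- Win ratio = wins / losses; net benefit = wins − losses

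Assume 28-day all-cause death of 24% v 18%, with a0 = 15% and a1 = 20%. Counting all deaths:

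- Wins = 0.24 × 0.82 + 0.76 × 0.82 × 0.15 × 0.80 = 0.1968 + 0.0748 = 0.2716
- Losses = 0.18 × 0.76 + 0.76 × 0.82 × 0.20 × 0.85 = 0.1368 + 0.1059 = 0.2427
- Win ratio = 1.119

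Subtracting the patients who die after discharge from p0 and p1:

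| Die after discharge (standard v individualised) | p0, p1 counted | Wins | Losses | Win ratio |
|---|---|---|---|---|
| None | 0.24, 0.18 | 0.2716 | 0.2427 | 1.119 |
| 2% v 2% | 0.22, 0.16 | 0.2634 | 0.2362 | 1.115 |
| 3% v 2% | 0.21, 0.16 | 0.2560 | 0.2392 | 1.070 |
| 3% v 1% | 0.21, 0.17 | 0.2530 | 0.2458 | 1.029 |

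If 1% to 3% of each arm die after discharge by day 28, 6 to 19 patients per arm are affected (630 × 0.01 and 630 × 0.03). The share of pairs containing at least one of them is 1 − 0.99² = 2% to 1 − 0.97² = 6%.

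**A second set of assumptions**

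Take death of 25% v 19% and non-fatal events in 30% of survivors in both arms. The win ratio counting all deaths is 1.222. If 5%, 10% or 20% of deaths in each arm follow discharge, it becomes 1.212, 1.202 or 1.182.

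With no true effect (25% v 25%), an unequal share of deaths after discharge moves the win ratio off 1.000. It is 1.087 if the shares are 5% standard and 15% individualised, and 0.920 if they are reversed.

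**The case against.** The strongest reply is that the document leaves the matter open. The sentences that set out the hierarchy say only mortality or death. The hospital limit comes from a table shell and from a sentence on safety reporting. All-cause death may be what is intended, and the full protocol is not shown. This stands in part: a reader might infer that the trial has settled on scoring post-discharge deaths as survivors, and the documents do not go that far. What they contain is a conflict between text and table, in which the only wording that specifies a setting is the hospital one.

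A second reply is that an in-hospital scope is coherent for a safety table, because non-fatal events are found by daily record review and contact with treating clinicians. That is a good reason for the lower tiers. It does not carry over to death, which is followed to day 90.

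Third, these deaths are not lost to the trial. They count in 90-day mortality, time to death and RRT-free days, and in the primary endpoint if they occur by day 14. This stands, and it confines the point to the safety composite.

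Three stronger readings should be resisted:

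- **Discharge practice in five countries biases the comparison.** Randomisation is stratified by site in permuted blocks, so differences in practice between sites and countries are balanced across arms. Only a difference between arms in discharge or post-discharge death could bias the result, and the documents give no figure for that.
- **Mortality decides about a third of all pairs.** This holds only for the assumed 24% v 18% (0.24 × 0.82 + 0.18 × 0.76 = 33%). The 14-day planning rates of 20% v 14% give 0.20 × 0.86 + 0.14 × 0.80 = 28%. The feasibility study's 13% v 6% gives 0.13 × 0.94 + 0.06 × 0.87 = 17%.
- **Table 1 says that day-28 mortality is collected in any location.** Its row says only mortality. That deaths outside hospital are captured is a fair inference from the all-cause 90-day outcome and the possible use of registries.

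**Conclusion.** The point holds as an inconsistency with a practical consequence. The text leaves the top tier unqualified, Table 5 and the Safety assessment wording place it in hospital, and following Table 5 treats a post-discharge death before day 28 as survival while RRT-free days scores it −1.

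On the assumed inputs the effect is negligible when post-discharge death is equal across arms (1.119 against 1.115). It becomes appreciable only when it differs by arm, for example 1.03 at 3% v 1%. No post-discharge rate is given, so these figures illustrate the mechanism and do not forecast a bias. The two-tier model also simplifies the real hierarchy. The primary endpoint, its analysis and the sample size are unaffected.

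The change is still worth making: it costs little and stops a post-randomisation event from cutting off the top tier.

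**What to change.** State in the Safety events text that the top tier of both the main and the sensitivity hierarchy is all-cause death by day 28 from randomisation, regardless of location. Make the mortality row that feeds the composite in Table 5 match, and adjust the table title so that the in-hospital limit applies to the non-fatal events only. Keep those in-hospital events as the lower tiers. Hospital mortality may still be shown as a separate descriptive row that does not enter the win ratio.

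The cost is one definition, one table row and a small change to a title. No new data should be needed, because day-28 status follows from the death dates required for time to death through day 90. The change should be recorded before any comparative safety results are seen.

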### Treatment separation between the two arms

A visual summary of MAP-deficit exposure and corresponding vasopressor dose management will be shown for both groups as a stacked bar plot (Figure S2) representing the percentage of time spent in the following mutually exclusive categories: MAP-deficit < 10%; 10–20% with vasopressor dose escalation; 10–20% without vasopressor dose escalation; > 20% with vasopressor dose escalation; > 20 to ≤ 30% without vasopressor dose escalation; and > 30% without vasopressor dose escalation. Differences between the two study arms for the percentage MAP deficit, percentage timepoints spent with more than 20% MAP-deficit, achieved MAP (including highest and lowest daily MAP) (Figure S3, S4) and vasopressor dose during the 5 days following randomisation will be estimated using linear mixed-effects models, with a random intercept for each patient and fixed effects for the treatment group, time since randomisation, noradrenaline-equivalent dose at randomisation, APACHE III score, site and type of shock. All non-missing observations in the period from randomisation to end of 4-hourly follow-up will be used. The effect estimate of interest will be the estimated difference in the marginal means for the two treatment groups from randomisation to day 5, displayed graphically, as well as in a table for 24, 48, 72 and 96 h after randomisation. Achieved MAP and percentage MAP-deficit over time can be presented visually with spaghetti plots with a random sample of patients overlayed with a loess smoother based on all patients.

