^**χ**^ % Time spent with > 20% MAP-deficit = [Σ(time-periods with > 20% MAP-deficit)/total time with available MAP data] × 100

^#^ Achieved-MAP was derived as the time-weighted average of 4-hourly values over the active treatment period

The time when a vasopressor or an inotrope agent is initiated will be identified as T0. Punctual four hourly interval data on MAP and norepinephrine-equivalent vasopressor dose [12] will be monitored until a patient is weaned off vasopressor or inotropic support for at least 24 h or up to a maximum of 5 days, whichever is earlier (Fig. 2). The time-weighted average MAP-deficit, while on vasopressor or inotropic support, will be reported for all patients as a measure of “relative hypotensive load” as described previously [8]. Percentage MAP deficit will be defined as the difference between pre-illness MAP and achieved MAP, divided by pre-illness MAP, expressed as a percentage. A more detailed explanation is provided in the supplement. Pre-illness MAP will be derived as a mean of up to 5 most recent, discrete, pre-illness MAP observations during the 3 years prior to illness, ascertained from past health records. Daily fluid balance and exposure to blood transfusions will also be recorded. Further, exposure to nephrotoxic agents within 14 days of randomisation will be monitored. Safety events such as atrial arrhythmia, ventricular arrhythmia, mesenteric ischemia, myocardial ischemia, Takotsubo cardiomyopathy, bilateral digital ischemia, cardiac arrest, ischemic stroke and haemorrhagic stroke during the study period will be monitored for all patients. Indications to initiate RRT such as presence of metabolic acidosis (pH < 7.2), blood urea nitrogen level of more than 30 mmol/l, hyperkalaemia (K > 6 mmol/l), creatinine level of > 499 micromoles/l, anuria for more than 6 h, fluid overload or other reasons such as toxin removal or clinician’s preference to start early RRT will also be recorded.

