**Fig. 2 Fig2:**
[figure not shown]
**a–c** Daily means and 95% confidence intervals for time-weighted average percentage MAP deficit, achieved MAP and noradrenaline-equivalent dose

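### The 5-day vasopressor-dose comparison uses only records kept until 24 h after weaning, so known zero doses are treated as missing and late means and the arm difference can be distorted

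*Protocol article*

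**What the plan says.** The Treatment separation section of the protocol article lists vasopressor dose among the measures to be compared over the 5 days after randomisation: "vasopressor dose during the 5 days following randomisation will be estimated using linear mixed-effects models". The model is specified "with a random intercept for each patient and fixed effects for the treatment group, time since randomisation", plus dose at randomisation, APACHE III score, site and type of shock. No treatment-by-time term is named. The target is the "estimated difference in the marginal means for the two treatment groups from randomisation to day 5", shown graphically and "in a table for 24, 48, 72 and 96 h after randomisation".

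The same section fixes the data that enter: "All non-missing observations in the period from randomisation to end of 4-hourly follow-up will be used". The Data collection section says when that follow-up stops. MAP and noradrenaline-equivalent dose are monitored every 4 h "until a patient is weaned off vasopressor or inotropic support for at least 24 h or up to a maximum of 5 days", whichever comes first.

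Nothing shown sets dose to zero after recording stops. The missing-data section says "MAP and percentage MAP deficit may be missing for some timepoints" and explains why the analysis tolerates this, but it does not mention dose. The caption of Fig. 2 announces "Daily means and 95% confidence intervals for time-weighted average percentage MAP deficit, achieved MAP and noradrenaline-equivalent dose" without stating a denominator. Table 1 marks vasopressor dose/use for the whole of Day 0–5. Table 3 separately lists a time-weighted average dose and the time to stopping vasopressors.

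**The concern.** The reported quantity is a 5-day comparison of all randomised patients. The data behind it cover patients on drug or within about a day of stopping. For MAP, a value after follow-up ends really is unknown. For dose it is not: while the patient is alive and off vasopressors, the dose is zero. The rule therefore discards known values, and discards them because the outcome has reached zero. If one arm weans later or runs at higher doses, the loss differs by arm.

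The background section names greater vasopressor use as a possible cost of the individualised strategy. This model is the article's time-resolved estimate of that cost. A table with negative mean doses at 72 or 96 h, or an exaggerated difference, would mislead readers about drug exposure.

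**Working it through.** **Plan's own figure.** The plan gives no number for the dose analysis. Its sample size, used below as the size of the main simulation, reproduces: 615 per arm for 20% v 14% (two-sided 0.05, 80% power), so 2 × 615 = 1230 and 1230 / (1 − 0.025) = 1262, against 1260 stated. The present point does not affect it.

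**Inputs.** From the article: 4-hourly records, stop after 24 h off support, 120 h horizon, patient random intercept, 1:1 allocation. Assumed, because the article gives none of it: median starting dose 0.15 mcg/kg/min, the shape of weaning, time on drug, the dose ratio between arms (1.0 to 1.3), and no restarts.

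**Step 1: raw means.** If every living patient without a record is at zero, then

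mean of recorded doses = true mean / share still recorded.

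With assumed median times on drug of 36 v 48 h and no deaths, 24% v 32% still have records at 96 h, and the recorded means are 0.061 v 0.072. The true means are 0.24 × 0.061 = 0.015 and 0.32 × 0.072 = 0.023. An average of recorded values alone is three to four times too high.

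**Step 2: the model.** Write dose(i,t) = a + b·arm + g(t) + covariates + u(i) + error. The time effect g(t) is common to all patients and u(i) only shifts the level. A patient already at zero is therefore projected to keep falling with everyone else. In the Step 1 example the 96 h marginal means were −0.041 v −0.025, against true values of 0.015 v 0.023.

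**Step 3: one scenario in full** (the one with most patients still recorded at 96 h; mcg/kg/min; standard / individualised / difference; both fits include treatment-by-time).

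| Time | Share recorded | Written rule | Zeros kept to 120 h |
|---|---|---|---|
| 24 h | 1.00 / 1.00 | 0.118 / 0.176 / 0.058 | 0.118 / 0.177 / 0.058 |
| 48 h | 0.87 / 0.92 | 0.069 / 0.121 / 0.052 | 0.074 / 0.124 / 0.050 |
| 72 h | 0.61 / 0.73 | 0.029 / 0.065 / 0.036 | 0.051 / 0.083 / 0.032 |
| 96 h | 0.41 / 0.55 | −0.010 / 0.026 / 0.035 | 0.034 / 0.060 / 0.025 |

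Keeping the zeros recovers the true 96 h means (0.034 and 0.060). Without a treatment-by-time term the model returns one difference for all four times: 0.0485 under the written rule and 0.0397 with zeros kept, a ratio of 1.22.

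**Step 4: other scenarios.** Overall (main-effect) arm difference, written rule v zeros kept:

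- Six scenarios, no deaths: 0.016 v 0.011 (1.5 times), 0.019 v 0.010 (1.9), 0.043 v 0.027 (1.6), 0.049 v 0.026 (1.9), 0.049 v 0.040 (1.2, the Step 3 case). With identical arms: −0.0035 v −0.0033, no material change.
- About 8% deaths by day 5, truncated at death, with two weaning shapes: 0.0166 v 0.0093 (1.78), 0.0191 v 0.0133 (1.44), 0.0411 v 0.0282 (1.46), 0.0562 v 0.0417 (1.35).
- Four weaning shapes, 400 per arm: about 1.3 to 2.0 times, absolute gaps about 0.004 to 0.025.
- A further run reached 2.4 times.

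In the six scenarios the 96 h marginal means ran from −0.155 to +0.031, against true means of 0.008 to 0.060, with 10–55% of patients per arm still recorded. With treatment-by-time, the 96 h differences were −0.039 v −0.001, 0.025 v 0.003, 0.012 v 0.009, 0.028 v 0.007 and 0.035 v 0.025. Single late time points can thus be further out than the overall coefficient, and not always upward.

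Most scenarios rest on one simulated data set, and some fits gave boundary warnings.

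**The case against.** **It is an estimand choice.** The intervention applies while vasopressors run, and the section says openly which records it uses, so a comparison during therapy may be intended. That would be legitimate if stated. But the text promises a difference to day 5, and the retained rows include up to 24 h of zeros after weaning, so they match neither a while-on-drug nor a full 5-day quantity.

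**Mixed models tolerate missing data.** Because 24 h of zeros are seen before recording stops, the loss can be called missing at random. That protects the estimate only if the model describes the unrecorded values correctly. A common linear time course with a patient-level shift does not know that dose stays at zero.

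**Zero-filling is a derivation detail for the full analysis plan.** Silence would be no finding. Here the article states which rows are used, and that rule produces the problem.

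**What stands.** Dose is not a primary or secondary outcome, and the DSMB's separation review is of MAP deficit. Table 3 reports average dose and time to cessation outside this model. Weaning removes no surviving patient's row before 24 h.

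Some stronger readings are tempting but not supported:

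- That Fig. 2 overstates dose as written: only its caption is visible, and the handling of weaned patients is not shown.
- That negative means are inevitable: with a plateau before weaning and 48 v 60 h on drug, the 96 h means were +0.022 and +0.065 (true 0.032 and 0.047).
- That restarts are certainly lost: the Data collection text implies it, but Table 1 marks dose for all of Day 0–5.
- That this model is the only measure of the vasopressor cost: Table 3 shows otherwise.

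**Conclusion.** The point holds as a conflict between a stated recording rule and a stated estimate. Known zeros are left out, and the model replaces them with a projected decline. From about 48 h the mean doses are unreliable and may be negative. The arm difference is distorted when the arms differ in dose or time to weaning, which is what the intervention might be expected to cause. In most simulated scenarios it was inflated, and the overall difference was roughly 1.2 to 2.4 times too large. That range rests wholly on assumed dose trajectories, weaning shapes and times on drug. If the arms are alike, the difference is little affected, although the late means are still wrong. The consequence is confined to a process measure: the mortality analysis is unaffected. It is worth correcting because the correction is cheap and the measure describes the strategy's stated trade-off.

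**What to change.** For the dose analysis in the Treatment separation section:

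1. Set noradrenaline-equivalent dose to 0 at every 4-hourly point from cessation to 120 h after randomisation while the patient is alive and off vasopressors. Do not fill after death.
2. Include a treatment-by-time term, so that the differences tabulated at 24, 48, 72 and 96 h can differ from one another.
3. Reconcile the stopping rule in Data collection with Table 1, so that doses are recorded if vasopressors restart before day 5.
4. Apply the same derivation to the dose panel of Fig. 2 if its daily means use the same truncated records.

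If a while-on-vasopressor comparison is really meant, say so and drop the description to day 5. That version compares patients selected by not yet having weaned, so the zero-filled series is preferable for total exposure.

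Cost: a sentence or two of analysis wording and a derivation from cessation times that Table 3 already requires. The one extra burden is recording dose for the few patients who restart. Recruitment is still open, so this can be arranged.

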### Data collection

Data will be tabulated for patient characteristics (Table 2) and process of care measures (Table 3). This table will include demographic data (age, sex), Acute Physiology and Chronic Health Evaluation (APACHE) III risk score [19], type of shock, comorbidities (chronic hypertension, diabetes mellitus, chronic obstructive pulmonary disease, ischemic heart disease, congestive heart failure, chronic kidney disease, valvular heart disease and peripheral vascular disease), organ system diagnosis (sepsis, gastrointestinal, respiratory, cardiovascular, neurological, renal, haematological, metabolic, musculoskeletal/soft tissue and other), pre-illness blood pressure, period (in weeks) between last pre-illness blood pressure measurement and randomisation, need for mechanical ventilation, volume of intravenous fluid administered within the prior 24 h, fluid balance, exposure to nephrotoxic agents (intravenous contrast, aminoglycoside, vancomycin, non-steroidal anti-inflammatory drug, ACE inhibitor or angiotensin receptor blocker, gancyclovir, calcineurin inhibitor, or remdesivir) within the prior 72 h, pre-morbid creatinine level, MAP at or closest to randomisation, serum lactate and serum creatinine levels obtained at or just prior to time of randomisation, time from ICU admission to randomisation (in hours) and the time from initiation of vasopressor therapy to randomisation (in hours).

**Table 2 Tab2:** Baseline characteristics

Characteristics	Standard MAP (*n* = xxx)	Individualised MAP (*n* = xxx)
Age, median [IQR], years		
Males, *n* (%)		
APACHE III score, median [IQR]		
Co-morbidities, *n* (%)		
Chronic hypertension		
Diabetes mellitus		
Chronic obstructive pulmonary disease		
Ischemic heart disease		
Congestive heart failure		
Chronic kidney disease		
Valvular heart disease		
Peripheral vascular disease		
Diagnosis organ system, *n* (%)		
Gastrointestinal		
Respiratory		
Cardiovascular		
Sepsis		
Neurological		
Renal		
Metabolic		
Musculoskeletal or soft tissue		
Haematological		
Other		
Type of shock, *n* (%)		
Septic		
Cardiogenic		
Mixed		
Other		
Period between pre-illness blood pressure (BP) measurements and randomisation, median [IQR], weeks		
Number of pre-illness BP readings per patient, *n* (%)		
2		
3		
4		
5		
Pre-illness mean arterial pressure, median [IQR], mmHg		
Receiving invasive mechanical ventilation at randomisation, *n* (%)		
MAP at randomisation, median [IQR], mmHg		

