### Interim analyses

The trial’s steering team will assess accrued adverse events at 10% and 25% of target patient recruitment (126 and 315 patients). The DSMB will review accrued data related to treatment separation (MAP deficit over time) and serious adverse events in both arms after enrolment of 630 participants (50% of the planned sample size). An additional analysis of the primary outcome measure of all-cause 14-day mortality will also be performed during this interim analysis. The study team and the DSMB will remain blinded to the group allocations. Arbitrary dummy group labels, e.g. “A” “B”, will be randomly assigned to the study groups for the interim analysis of the primary outcome variable and different labels, e.g. “G”, “F”, will be assigned to study groups for the analysis of treatment separation. The trial will not be stopped for futility. Following the review of safety events, the DSMB will be required to make a consensus recommendation regarding continuation, modification, or early termination of the trial. In case a consensus decision is unable to be reached, then the DSMB can request an additional interim analysis for further data.

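### The treatment-separation model has no treatment-by-time term, so its promised differences at 24, 48, 72 and 96 h are one coefficient repeated four times

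*Protocol article*

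**What the plan says.** The section headed Treatment separation between the two arms covers percentage MAP deficit, time points with more than 20% deficit, achieved MAP and vasopressor dose over the five days after randomisation. Differences between arms "will be estimated using linear mixed-effects models". The section then sets out their terms, starting "with a random intercept for each patient and fixed effects for the treatment group, time since randomisation, noradrenaline-equivalent dose at randomisation". The rest of the covariate list reads "noradrenaline-equivalent dose at randomisation, APACHE III score, site and type of shock". No interaction is named.

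The section then defines its estimand: "The effect estimate of interest will be the estimated difference in the marginal means for the two treatment groups from randomisation to day 5". The output is to be "displayed graphically, as well as in a table for 24, 48, 72 and 96 h after randomisation".

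Three other places bear on the point:
- Data collection says that 4-hourly recording runs until the patient has been off support for at least 24 h, or to 5 days if that comes first. Table 2 there includes "MAP at randomisation, median [IQR], mmHg".
- The Fig. 2 caption describes daily means with 95% confidence intervals for time-weighted MAP deficit, achieved MAP and noradrenaline-equivalent dose.
- Interim analyses says "The DSMB will review accrued data related to treatment separation (MAP deficit over time" at 630 patients.

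**The concern.** The listed terms and the promised output do not fit together. A table at four times and a graph over five days make sense only if the difference may vary with time, and the listed model does not allow that.

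Constant separation should not be assumed in this design. The individualised target applies only while vasopressors run, clinicians may tailor or step it, and recording continues for a day after weaning. Patients also leave the data as they wean, so early readings outnumber late ones and weigh more in a single coefficient.

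Separation matters for reading a neutral mortality result. It helps to tell a strategy that did not work from targets that were not sustained. A model-based figure at 96 h that mostly reflects the first days would not serve that purpose.

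**Working it through.** **Plan's own figure.** The plan gives no number for separation. Its one design figure reproduces but plays no part here: 20% versus 14%, two-sided alpha 0.05 and 80% power need 615 per arm, 1230 in total, and 1230 / 0.975 = 1262 against 1260 stated.

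**Algebra.** Write the listed model for patient i at time t, with g = 1 for the individualised arm:

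Y = b0 + b1·g + f(t) + covariates + u_i + e

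Difference in marginal means at t = [b0 + b1 + f(t)] − [b0 + f(t)] = b1.

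The time function cancels, whether it is linear, categorical or a spline. So the entries at 24, 48, 72 and 96 h all equal b1, with one standard error, and the graph of the difference is flat. With a product term g·h(t), the difference becomes b1 + h(t) and can vary.

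**Illustration A (assumed values, one simulated data set).** 1260 patients; 4-hourly MAP; true separation 10 − 8t/120 mmHg, falling from 10 to 2 over 120 h; between-patient SD 6; residual SD 6; exponential follow-up with mean 60 h. Under that follow-up, exp(−24/60) = 67% of patients are still observed at 24 h and exp(−96/60) = 20% at 96 h. Random-intercept models gave, in mmHg (SE):

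| Time | True | Group + time (linear or categorical) | Group × time (linear) |
|---|---|---|---|
| 24 h | 8.4 | 7.74 (0.359) | 8.13 (0.358) |
| 48 h | 6.8 | 7.74 (0.359) | 6.54 (0.363) |
| 72 h | 5.2 | 7.74 (0.359) | 4.95 (0.387) |
| 96 h | 3.6 | 7.74 (0.359) | 3.37 (0.427) |

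- Ratio at 96 h: 7.74 / 3.6 = 2.15.
- 95% interval at 96 h, main effects: 7.74 ± 1.96 × 0.359 = 7.04 to 8.44, which excludes 3.6.
- 95% interval at 96 h, interaction: 3.37 ± 1.96 × 0.427 = 2.53 to 4.21, which includes it.
- Overall effect: the true differences at the four times average (8.4 + 6.8 + 5.2 + 3.6) / 4 = 6.0, against 7.74. The single coefficient is a data-weighted average tilted towards early times.

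**Illustration B (a different assumed pattern).** 600 patients, follow-up averaging about 60 h, and true differences of 9.4, 6.3, 4.2 and 2.8 mmHg, which match 14·exp(−t/60). The main-effects model gave 8.7 at all four times. Ratio at 96 h: 8.7 / 2.8 = 3.1.

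**Baseline MAP.** In illustration A, baseline MAP was set to the patient's level plus noise of SD 5. Adding it moved the main-effects estimate little (7.74 to 7.67) and cut the SE from 0.359 to 0.262, a variance reduction of 1 − (0.262/0.359)² = 47%. That rests on a strong assumed link. For assumed correlations of 0.3 to 0.5, the between-patient variance falls by about r², or 9% to 25%. Adding baseline MAP does not make the difference vary with time.

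**The case against.** The strongest reply is that the interaction is implied. The requested output makes sense only if the difference may change, and a journal article condenses a fuller plan. That may well be what the authors intend. But the article says that it publishes the pre-specified analysis plan, the terms are enumerated, and they conflict with an output stated in the same section. This goes beyond an omitted detail, though one line settles it.

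A reader might infer more than the document supports:
- **That fading separation would be hidden.** It would not be. The daily means and intervals in Fig. 2 do not depend on this model, and the section allows patient-level plots with a smoother based on all patients. The fault is confined to the model-based table and graph, which could then disagree with those displays.
- **That the DSMB would be misled.** Interim analyses does not say that its review of MAP deficit over time uses this model.
- **That late separation is overstated.** This holds only if separation wanes. If it grows, a constant understates it. No document gives the pattern.
- **That leaving out baseline MAP biases the comparison.** Under randomisation it costs precision only. The model already includes the baseline of the vasopressor-dose outcome.

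**Conclusion.** The point holds as a conflict between a stated model and its stated output. That the four differences are equal is algebraic and rests on no assumption beyond the listed terms.

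The size of the error cannot be fixed from the document. The two- to threefold excess at 96 h comes from two assumed waning patterns and an assumed mean follow-up of 60 h, and it would be nil if separation were constant. This is a process measure: the primary and secondary outcome models do not use it, and the per-protocol and as-treated groupings use observed means. It is worth correcting because the model-based difference is the declared effect estimate for separation. Baseline MAP is a secondary matter of precision.

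**What to change.** 1. Add a treatment-by-time interaction to the separation models, with time categorical (by day or 4-hourly block) or as a spline. Take the 24, 48, 72 and 96 h contrasts from it.
2. Define the overall effect as the average of the contrasts over a stated set of times, so that the weighting does not depend on who is still being recorded.
3. As a secondary improvement, add MAP (or MAP deficit) at randomisation as a fixed effect in the MAP-based models. Data collection allows the reading closest to randomisation, so specify one taken before the allocated target is applied.

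This changes analysis wording only, with no new data and no change in sample size. The cost is wider late intervals: in illustration A the SE at 96 h rose from 0.359 to 0.427, or 19%. A categorical or spline form may widen them further than the linear term used there.
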